### Data collection and management

4.9

This RCT uses multiple diagnostic tools to assess ear health and function for outcome evaluation. The hearScope™ video-otoscopy device visualizes the external auditory canal and tympanic membrane, whilst tympanometry using the Interacoustics Titan Middle Ear Analyzer detects middle ear fluid causing conductive hearing loss [46,47]. Hearing sensitivity levels (pure-tone audiometry) are tested using the hearScreen® Smartphone Screening Audiometer [48], and the Interacoustics Titan Middle Ear Analyzer assesses inner ear health (cochlea outer hair cell function) via otoacoustic emissions to identify sensorineural hearing loss [49].

The OM-6 questionnaire evaluates health-related QoL in children with recurrent OM [50], and the PLUM and HATS are culturally appropriate questionnaires which aid in early detection of hearing and speech issues by gauging parent/carer perceptions of their child's hearing and speech [51,52]. A motivational outcomes questionnaire, developed using components of the Self Determination Theory Treatment Self-Regulation Questionnaire and the Perceived Competence Scale, measures the autonomous motivation of families to complete their assigned program, their perceived confidence and self-efficacy relating to program participation, and the extent to which its outcomes have met their expectations using a seven-point Likert scale [53].

In line with the RE-AIM framework, used in public health and implementation science to assess the impact and sustainability of health interventions, data to assess the implementation fidelity of the BBC intervention plus hand hygiene within the RCT will be collected using structured checklists [54]. These checklists include the assessment of the quality of intervention delivery at enrolment and quality of intervention performance at enrolment and post-randomization, along with a parent/carer checklist to confirm their level of understanding of the intervention at enrolment (Table 2) [54].

All research staff receive specialist training in study procedures (clinical and non-clinical) to ensure accuracy and reliability, along with International Council for Harmonization Good Clinical Practice (ICH-GCP) training to uphold standards in ethical conduct, data handling, and participant safety [55].

Data is collected using physical forms, securely stored at The Kids Research Institute Australia, and secure electronic devices store de-identified otoscopy, tympanometry, audiometry, and otoacoustic emissions data on HearX and Titan Suite servers. All data is transferred to Electronic Case Report Forms in the REDCap database, with accuracy of data entry ensured through double-checking and verification processes.

### Primary and secondary statistical methods

4.10

A Bayesian logistic regression model will be used for the primary analysis on the binary endpoint $Y_{i}\in \left\{0,1\right\}$ for participant i=1,2,…,N. Currently, there are two arms and three recruitment pathways, however the model is designed to allow additional arms or recruitment pathways to be introduced in the future. A participant may be randomized to arm j=0,1,…,J (where j=0 is the control arm and j=1 is the intervention arm) and be recruited via pathway r=0,1,…,R (where r=0 is the PCH otolaryngology/audiology outpatient departments, r=1 is the PCH otolaryngology surgical pathway, r=2 is Djaalinj Waakinj and r≥3 for other approved sites). Let $x_{i}$ and $\omega_{i}$ be vectors of length J and R and contain the arm allocation and recruitment pathway, respectively, for participant i. Here, $x_{ij}=1$ if participant i is allocated to arm j and $x_{ij}=0$ otherwise. Similarly, $\omega_{ir}=1$ if participant i is recruited via recruitment pathway r and $\omega_{ir}=0$ otherwise. We use a Bernoulli model with a logistic link function below:$$Y_{i}∼\text{Bernoulli}\left(\text{logi}t^{-1}\left(\pi_{i}\right)\right)$$$$\pi_{i}=\alpha +\sum_{j=1}^{J}x_{ij}\beta_{j}+\sum_{r=1}^{R}\omega_{ir}\gamma_{r}$$

Here, $\pi_{i}$ is the log odds of OME resolution between 4 and 6 weeks post-randomization for participant i. The log odds for a participant allocated to the control arm and recruited via the PCH otolaryngology/audiology outpatient pathway is α, and $\beta_{j}$ and $\gamma_{r}$ are the adjusted log odds ratios of arm j compared to the control arm and recruitment pathway r compared to the PCH otolaryngology/audiology outpatient pathway, respectively. We assign the following weakly informative prior probability distributions to the model parameters:$$\alpha ∼N\left(\text{logit}\left(0.17\right),0.3^{2}\right)$$$$\beta_{j},\gamma_{r}∼N\left(0,1\right)\;\forall j=1,\ldots ,J,r=1,\ldots ,R$$

The posterior distribution of the quantity of interest ($\beta_{1}$) will be estimated from the primary analysis and will be used to inform trial adaptation decisions.

Statistical analyses for secondary outcome measures will involve using descriptive statistics to estimate rates of natural OME resolution from tympanometry results indicating OME persistence or resolution, analyzed using data collected during eligibility screening prior to enrolment and from control arm participants. Discharge rates from otolaryngology and audiology care will be tracked as percentages for both arms. Hearing outcomes will be compared using changes from baseline (week 0) in the four-frequency average hearing thresholds to those at weeks 4-to-6 and 24-to-32, analyzed using Bayesian linear models adjusted for baseline and recruitment site. QoL will be evaluated by analyzing changes in OM-6 outcomes using descriptive statistics, whilst PLUM and HATS outcomes will undergo additional analysis using a Bayesian proportional odds model. An economic analysis will compare costs of diagnosing and managing OME in the RCT as opposed to standard care, evaluating per-patient costs for OME diagnosis, tympanometry tube insertion, and cost benefits measured by OME resolution rates in AUD. High-throughput qPCR on the BioRad CFX96 platform will measure bacterial loads and otopathogen densities associated with OME *(Hemophilus influenzae, Streptococcus pneumoniae, Moraxella catarrhalis, Staphylococcus aureus, and Group A Streptococcus)* using validated qPCR primers, probes and reaction conditions [[56], [57], [58]]. The changes in bacterial densities over time between study arms will be ascertained through statistical analysis, assessing reductions or increases in bacterial load for each species of interest. Adverse events will be analyzed based on their number and nature in both trial arms. To align with the trial's flexible approach to study appointments, any results obtained outside of scheduled time points will be subject to sensitivity analyses to assess their impact on primary and secondary outcomes.

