The 'Blow, Breathe, Cough’ (BBC) intervention is a simple, freely available, school and family led health promotion intervention encouraging children to blow their nose, breathe deeply, cough, and practice good hand hygiene to assist nasal and respiratory secretion clearance, ultimately encouraging middle ear fluid drainage [28]. Although used anecdotally since the 1970s in Australian classrooms, primary care settings, and Aboriginal community health organizations to prevent ear disease, the BBC intervention plus hand hygiene lacks robust evidence on its efficacy [29]. Findings from interviews with Australian educators and primary healthcare workers suggest the BBC intervention plus hand hygiene may reduce OME and improve hearing in children, decrease the incidence of ear infections, and increase knowledge and awareness of positive hygiene practices [29,30]. Additionally, a non-randomized controlled trial conducted in a school setting demonstrated a statistically significant reduction in signs of upper and lower respiratory tract disease following a daily program of nose blowing, deep breathing, coughing, and exercise among Aboriginal children, although maintaining daily compliance was challenging due to inconsistent school attendance [31]. Considered together, these studies provide preliminary support for evaluating the treatment efficacy of the BBC plus hand hygiene intervention in resolving OME using a randomized-controlled trial (RCT) in a home-based setting. This paper details the protocol for a RCT that will examine the efficacy of the BBC intervention plus hand hygiene in resolving (treating) OME in children in a home-based setting and its impact on hearing, speech, and quality of life (QoL) outcomes.

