Secondary outcome measures include: (1) rate of natural OME resolution, evidenced by a transition of type B tympanograms to type A or C tympanograms; (2) proportion of otolaryngology/audiology care discharges, evaluated using multidisciplinary team (MDT) and clinician review outcomes from enrolment to final follow-up (weeks 24-to-32); (3) family satisfaction with care provision through the RCT, assessed using a survey at final follow-up, (4) four-frequency hearing thresholds measured by audiometry at enrolment, post-randomization, and final follow-up; (5) QoL, assessed through the Otitis Media-6 (OM-6), Parent-evaluated Listening and Understanding Measure (PLUM), and Hearing and Talking Scale (HATS) questionnaires at enrolment, post-randomization, and final follow-up; (6) bacterial loads, quantified as the densities of all bacteria species of interest at enrolment and post-randomization, analyzed using high-throughput qPCR on samples collected from the nasopharynx and palms of hands; (7) cost-of-service comparison for OME diagnosis and management through the study compared to standard care via economic analysis; and (8) the proportion of adverse events, monitored through safety data collection from enrolment to final follow-up. Refer to Table 2 for a comprehensive schedule of data collection methods and collection timepoints for participants in both trial arms.

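### OM-6, the only questionnaire described as measuring health-related QoL, is evaluated by descriptive change scores alone, with no between-arm estimate or interval named

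*Protocol article*

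**What the plan says.** The aim is in section 3.1 (Background and rationale): the trial will examine the efficacy of the intervention and "its impact on hearing, speech, and quality of life (QoL) outcomes". The abstract also lists QoL among the effects to be evaluated.

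Section 4.5 (Outcomes) defines the fifth secondary outcome as "QoL, assessed through the Otitis Media-6 (OM-6), Parent-evaluated Listening and Understanding Measure (PLUM), and Hearing and Talking Scale (HATS) questionnaires", measured at enrolment, post-randomization and final follow-up. Table 2 marks all three questionnaires as mandatory at each of these visits.

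Section 4.9 (Data collection and management) describes the instruments differently. It says "The OM-6 questionnaire evaluates health-related QoL in children with recurrent OM", and it describes PLUM and HATS as "gauging parent/carer perceptions of their child's hearing and speech".

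Section 4.10 (Primary and secondary statistical methods) then assigns the analyses:

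- OM-6: "QoL will be evaluated by analyzing changes in OM-6 outcomes using descriptive statistics".
- PLUM and HATS: "PLUM and HATS outcomes will undergo additional analysis using a Bayesian proportional odds model".
- Hearing thresholds, as change from week 0 to each follow-up: "analyzed using Bayesian linear models adjusted for baseline and recruitment site".

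**The concern.** An effect of the intervention on QoL is a comparison between arms, and it needs an estimate with a measure of uncertainty. For OM-6 the plan names neither. The wording of section 4.10 separates OM-6 from the two questionnaires that receive further analysis, so this is a stated choice of method and not a detail left for later.

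At stake is how the trial can report on health-related QoL. With descriptive changes only, readers would compare two columns of mean changes by eye. Any contrast calculated afterwards would be chosen after the data were seen. If that contrast were a plain difference in change scores, it would also leave unused the relation between baseline and follow-up OM-6, which the hearing analysis does use.

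**Working it through.** **1. The analyses side by side (section 4.10, with Table 2 for data collection)**

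| Measure | Described in section 4.9 as | Collected at week 0, weeks 4-6 and weeks 24-32 | Analysis named |
|---|---|---|---|
| Hearing thresholds | hearing sensitivity | yes | Bayesian linear model, adjusted for baseline and site |
| PLUM, HATS | parent or carer view of hearing and speech | yes | Bayesian proportional odds model, covariates not stated |
| OM-6 | health-related QoL | yes | descriptive statistics on changes |

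OM-6 is the only one of these measures without a model, and the only one described as measuring health-related QoL. Its baseline value is mandatory data. Site is a randomization stratum (section 4.8), so it is recorded for every child. The article gives no reason for treating OM-6 differently.

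**2. Is there a plan figure to reproduce?** No. The article gives no standard deviation, target difference, correlation or power for OM-6. Everything below is illustrative.

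**3. What baseline adjustment is worth**

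Assume the same standard deviation σ at baseline and follow-up, and a correlation r between them. The value of r is assumed, because the documents do not give it. The comparison is with an unadjusted difference in change scores between arms. The plan does not name that contrast, but it is the one its descriptive changes would invite.

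- Change score, variance per child: σ² + σ² − 2rσ² = 2(1 − r)σ²
- Baseline-adjusted, variance per child: (1 − r²)σ²
- Ratio of adjusted to change score: (1 − r²) / [2(1 − r)] = (1 + r)/2

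With 125 children per arm (the maximum of 250 in section 4.6, allocated 1:1, all with OM-6 data), the difference detectable with 80% power at two-sided 5% is (1.96 + 0.84) × √(variance × 2/125), in units of σ. The number of children that change scores would need to match the adjusted analysis of 250 is 250 divided by the ratio.

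| Assumed r | Change score 2(1 − r) | Adjusted 1 − r² | Ratio | Variance saved | Detectable difference, change score → adjusted | Children needed by change scores |
|---|---|---|---|---|---|---|
| 0.3 | 1.40 | 0.91 | 0.65 | 35% | 0.42 → 0.34 SD | 385 |
| 0.5 | 1.00 | 0.75 | 0.75 | 25% | 0.35 → 0.31 SD | 333 |
| 0.7 | 0.60 | 0.51 | 0.85 | 15% | 0.27 → 0.25 SD | 294 |

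Worked line for r = 0.5: 2(1 − 0.5) = 1.00; 1 − 0.25 = 0.75; 0.75/1.00 = 0.75; 250/0.75 = 333.

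The gain shrinks as r rises. The absence of a named contrast and interval does not depend on r.

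**The case against.** The strongest objection is that section 4.5 defines the QoL outcome as OM-6, PLUM and HATS together, and two of the three are modelled. This stands, and it limits the point. A reader might infer that the whole QoL objective ends without a between-arm analysis. The documents do not support that: the gap concerns OM-6, and with it the one instrument described as measuring health-related QoL.

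Second, the percentages compare an adjusted analysis with a contrast that the plan never names, at an assumed correlation. This also stands. They show what adjustment could add and do not measure an error in a planned result.

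Third, describing one secondary questionnaire is defensible in a trial powered only on OME resolution, and descriptive statistics could include arm means with intervals, set out in a fuller document. This stands in part. Such a layout is possible, but the article says that PLUM and HATS receive a model in addition and says nothing of the kind for OM-6. A modelled OM-6 contrast would therefore go beyond the stated method.

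Fourth, the article gives no scoring or distribution for OM-6, so nothing in it shows that a linear model must be used. This stands, and the fix leaves the form open.

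A reader might also extend the point to discharge from care, where "Discharge rates from otolaryngology and audiology care will be tracked as percentages for both arms". The documents do not support this. Percentages by arm already permit a risk difference, and site is already a randomization stratum. The precision formula above is for a continuous outcome and does not carry over to a logistic model.

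**Conclusion.** The point holds for OM-6. The plan fixes descriptive change scores as its only analysis and names no between-arm estimate or interval. Yet the effect on QoL is a stated aim, and the companion questionnaires and hearing are modelled from the same visits.

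The possible gain in precision is 35%, 25% or 15% less variance at r = 0.3, 0.5 or 0.7. This assumes equal standard deviations at the two times and takes an unadjusted change-score contrast as the comparator. The detectable differences also assume OM-6 data on all 250 children, and would be larger if recruitment stopped early.

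This is a weakness in one instrument of one secondary outcome. No decision rule in section 4.11 uses OM-6, and the primary analysis and sample size do not change.

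**What to change.** Amend the OM-6 sentence in section 4.10, and any matching text in the full protocol or analysis plan, to say:

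- OM-6 at weeks 4-6 and at weeks 24-32 is analysed with a Bayesian model that contains arm, baseline OM-6 and recruitment site.
- The form is the linear model already planned for hearing or, if the score distribution calls for it, the ordinal form planned for PLUM and HATS, with baseline OM-6 named as a covariate. The criterion for choosing between them is stated in advance.
- The arm difference (an odds ratio under the ordinal form) is reported with a 95% credible interval, and the descriptive summaries are kept alongside.

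Under the linear form the change-from-baseline wording can stay. Once baseline is a covariate, the arm difference is the same whether the response is the follow-up score or the change.

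The cost is a few lines of text and one more model of a kind already planned. It needs no new data, visits or children. The change should be made before OM-6 results by arm are seen.

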### Interim analysis and decision criteria

4.11

The RCT will involve regular Bayesian updates to assess pre-planned decision criteria efficiently, ensuring timely answers to research questions [59]. The pre-planned adaptations include stopping recruitment for superiority or futility based on the primary analysis. The first interim analysis will occur after 100 eligible participants have completed the four-to-six-week post-randomization follow-up (referred to as ‘completers’), and subsequent updates for every 50 additional completers for the remainder of the RCT. Only data for eligible participants reaching weeks 4-to-6 will be used in the primary analysis.

Decision criteria for superiority and futility were identified using trial simulation to control for power and type one error. The BBC intervention plus hand hygiene will be declared superior at a pre-specified analysis, and recruitment into the trial may stop if the decision ruler for superiority is met:$$P\left(\beta_{1}>\log\left(1.1\right)\right)>0.975$$

Alternatively, at a pre-specified analysis, the trial may stop recruitment for futility if the decision rule for futility is met:$$P\left(\beta_{1}>\log\left(1.1\right)\right)<0.05$$

### Clinical oversight

4.12

For participants recruited through Western Australian pediatric hospital pathways, a multidisciplinary team (MDT) structure will be utilized to review the clinical progress of each participant. The MDT consists of an otolargyngology Clinical Nurse Specialist, Consultant/Registrar, and Audiologist from each participating health service, as well as a study researcher, who collectively review clinical findings and formulate a care plan that aligns with the 2020 Otitis Media Guidelines [4], enabling alteration, escalation, or discharge from care to occur as clinically appropriate. Following the MDT review, care plans are delivered to parent(s)/carer(s) via phone call. For participants recruited through the Djaalinj Waakinj pathway, Research Audiologists provide ongoing clinical oversight to ensure care provided through the study aligns with the 2020 Otitis Media Guidelines [4].

### Community consultation

4.13

In Australia, there is a prominent focus on research efforts dedicated to improving the health and wellbeing of Aboriginal people and communities in response to their experiences of ongoing health inequities. These inequities stem from the enduring impacts of colonization, including displacement, loss of cultural foundations, and systemic socioeconomic disadvantage [60,61]. Despite this focus, research involving Aboriginal people in Australia has a complex history of exploitation, misrepresentation, and marginalization [61]. In recent decades, approaches to research in the Aboriginal space have begun to shift from the treatment of Aboriginal people and communities as research subjects towards their inclusion as active partners and key stakeholders throughout the research process [43,44,61]. This shift is driven by researchers, organizations, and guidelines that acknowledge and understand the importance of adopting ethical, community-driven approaches that prioritize self-determination, foster genuine collaboration, and uphold cultural respect, resulting in research outputs that are both beneficial and culturally responsive [43,44,61].

The RCT is guided by an Aboriginal Community Advisory Group (ACAG), consisting of community members representing the south metropolitan area of Perth, Western Australia. The ACAG emphasized the importance of prioritizing research on childhood ear disease that focuses on reducing hospital visits, minimizing medication use, and avoiding surgical interventions. Recognizing the potential of the BBC plus hand hygiene to achieve these priorities, the ACAG endorsed conducting a RCT to test its efficacy. The research team provides regular updates to the ACAG about the progress of the RCT, incorporating their feedback to ensure the perspectives of Aboriginal children and families are upheld in all facets of research conduct. The ACAG's efforts highlight the critical role of culturally appropriate, community-driven health research in achieving meaningful outcomes for Aboriginal communities [43]. Given the diverse nature of communities across WA, in-depth community consultation with appropriate local community members and organizations will be conducted prior to adding any new WA study sites.

Additionally, The Kulunga Aboriginal Research Unit at The Kids Research Institute Australia continue to provide guidance, cultural expertise, and community navigation support to ensure this trial meets the standards for Aboriginal Health Research [62].

### Data and participant safety monitoring

4.14

As rationalized by the NHMRC (2018) guidelines on Data Safety Monitoring Boards (DSMBs), a DSMB will not be convened as the BBC intervention plus hand hygiene and RCT procedures pose no significant risks to participants [63,64]. To maintain trial oversight, a Trial Advisory Group (TAG), comprising of key investigators, study staff, and an external advisor oversee the study, reviewing progress and addressing highlighted issues on a quarterly basis. An independent statistician will review the interim analyses data and share outcomes with the TAG for evaluation against decision criteria.

Safety data will be gathered at routine study visits through participant self-reporting and clinician/researcher observations. Any Adverse Events or Serious Adverse Events will be promptly reported following NHMRC guidelines to maintain participant safety and study integrity [64].

